#### Economic evaluation

The aim of the economic evaluation is to relate the difference in societal costs between BA and TAU to the difference in clinical effects. Both a cost-effectiveness and a cost-utility analysis will be performed with a time horizon of 12 months. The analysis will be performed in accordance with the intention-to-treat principle. Missing cost and effect data will be imputed using multiple imputation. Bivariate regression models will be used to estimate cost and effect differences between the groups while adjusting for relevant confounders. Incremental cost-effectiveness ratios (ICERs) will be calculated by dividing the difference in mean total costs between the two treatment groups by the difference in mean effects. Bias-corrected accelerated bootstrapping with 5000 replications will be used to estimate 95% confidence intervals around cost and effect differences, and uncertainty around the ICERs. Uncertainty surrounding ICERs will be graphically presented on cost-effectiveness planes. Cost-effectiveness acceptability curves will also be estimated showing the probability that BA is cost-effective in comparison with TAU for a range of different ceiling ratios thereby showing decision uncertainty [80].

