## Methods

### Study design

The design of this study is a cluster randomized controlled multicentre trial with two parallel treatment groups with a follow up of 52 weeks. The treatment conditions are behavioural activation (BA), and treatment as usual (TAU). Data are collected at general practices in the South-Eastern region of the Netherlands. Only practices that employ a mental health nurse (MHN) are included. Currently, more than 80% of Dutch PCCs employ an MHN [44]. A list of currently participating PCCs can be found on http://beatdepressie.nl/voor-deelnemers/. We will report the study according to the SPIRIT guidelines [45]. The study has been approved by the local medical ethical committee of the Radboud University Medical Centre (CMO Arnhem-Nijmegen).

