### Sample size

Comparing the effects BA for depression to a waiting list condition, Cuijpers et al. reported an effect size of 0.9 in a meta-analysis [27]. Since we will be comparing BA to a more active treatment condition (TAU) in depressed older patients, we estimate the effect size for depression outcome of BA versus TAU to be 0.50, a modest but clinically relevant value. Based on this estimate (alpha = 0.05, power (beta) = 0.80, 2-tailed test) and data clustering within PCCs (ICC of 0.05 and a cluster size of *n* = 6) 100 patients are required per group with two groups of 14 clusters (based on 14 potential patients per PCC and a 50% refusal and a 20% dropout rate).

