### Assignment of interventions

PCCs are the units of randomization. PCCs that employ the same MHN will be in the same treatment condition, preventing contamination. An independent statistician will use pairwise matching to randomize the PCCs, taking into account the amount of MHNs in a PCC, as well as the sex of the MHN and the size of the patient population. In half of the PCCs the MHNs are trained to give BA-treatment while the other half will treat patients as usual. GPs, patients and MHNs are not blinded to treatment condition because PCCs are the units of randomisation, but the research assistants that assess depression after treatment are blind to condition.

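### The economic analysis is specified without a practice level in a cluster-randomised trial; if run at patient level, its intervals and acceptability curves would overstate certainty whenever costs or QALYs correlate within practices

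*Protocol article*

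**What the plan says.** The Study design section describes a "cluster randomized controlled multicentre trial with two parallel treatment groups with a follow up of 52 weeks". Under Assignment of interventions, "PCCs are the units of randomization", practices sharing a mental health nurse go to the same arm, and "An independent statistician will use pairwise matching to randomize the PCCs" on number and sex of nurses and size of the patient population. The Sample size section allows for "data clustering within PCCs (ICC of 0.05", with a cluster size of 6.

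Under Statistical analyses, Economic evaluation, three steps carry the inference:
- Imputation: "Missing cost and effect data will be imputed using multiple imputation".
- Estimation: "Bivariate regression models will be used to estimate cost and effect differences between the groups while adjusting for relevant confounders".
- Uncertainty: "Bias-corrected accelerated bootstrapping with 5000 replications will be used to estimate 95% confidence intervals around cost and effect differences, and uncertainty around the ICERs".

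Cost-effectiveness planes and acceptability curves follow from these. No step mentions the practice, the matched pairs or the resampling unit. By contrast, the Clinical outcomes paragraph names mixed linear regression, and the Process variables and predictors paragraph names multilevel mediation models.

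**The concern.** Patients in one practice share GPs, a nurse and a local way of working. Usual care is left to the GP, and the costs counted include consultations, medication and admissions, so correlation of costs within practices is plausible. A patient-level bootstrap treats such patients as independent. A regression without a practice term does the same, and an imputation model without the practice tends to dilute the practice effect in the filled-in values.

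Cost-effectiveness is one of the two parts of the primary objective and the second main research question. The acceptability curves are there to show how sure a decision-maker can be, and that is what ignoring clustering distorts: probabilities are pushed away from 0.5, in whichever direction the estimate points.

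**Working it through.** **1. Reproduce the plan's own figure.** Inputs from the Sample size section: standardised effect 0.50; "alpha = 0.05, power (beta) = 0.80, 2-tailed test"; ICC 0.05; cluster size m = 6; dropout 20%.
- Individually randomised: n = 2 × ((1.960 + 0.842)/0.50)² = 62.8, so 63 per arm.
- Design effect DE = 1 + (6 − 1) × 0.05 = 1.25; 63 × 1.25 = 78.75, so 79.
- Dropout: 79/0.80 = 98.75, so 99 per arm, against 100 stated.
- Without the design effect: 63/0.80 = 78.75, so 79 per arm.

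The stated 100 therefore needs the design effect. For depression, the protocol itself treats clustering as non-negligible.

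**2. Carry the same design effect to the economic intervals.** The protocol gives no ICC for costs or QALYs, so using 0.05 is an assumption. A standard error that ignores clustering is too small by a factor √DE. The interval is too narrow by 1 − 1/√DE, and a nominal 95% interval covers 2Φ(1.96/√DE) − 1. At m = 6:

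| ICC (assumed for costs and QALYs) | DE | √DE | Too narrow by | Coverage |
|---|---|---|---|---|
| 0 | 1.00 | 1.000 | 0% | 95.0% |
| 0.01 | 1.05 | 1.025 | 2.4% | 94.4% |
| 0.05 | 1.25 | 1.118 | 10.6% | 92.0% |
| 0.10 | 1.50 | 1.225 | 18.4% | 89.0% |
| 0.20 | 2.00 | 1.414 | 29.3% | 83.4% |

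The cluster size matters little. An intention-to-treat analysis with imputation would include all those enrolled, 200/28 = 7.14 per practice; at ICC 0.05 that gives DE 1.307, intervals 12.5% too narrow and coverage of 91.4%.

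**3. Acceptability probabilities.** With net benefit approximately normal, a reported probability p becomes Φ(Φ⁻¹(p)/√DE). At ICC 0.05 and m = 6, 0.95 becomes Φ(1.645/1.118) = 0.929, and 0.90 becomes Φ(1.282/1.118) = 0.874.

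**4. Simulation of the bootstrap.** Set-up: 14 clusters of 6 per arm, normal data, no matching, no missing data, 1500 trials, 600 replicates each, Monte Carlo error about 0.7 percentage points. Coverage of the nominal 95% BCa interval:

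| ICC | Patients resampled | Practices resampled |
|---|---|---|
| 0 | 94.3% | 92.9% |
| 0.05 | 91.0% | 92.3% |
| 0.10 | 89.2% | 93.3% |

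The patient-level column agrees with the formula to within about one point. Plain practice resampling also falls short of 95% with 14 clusters per arm, so replacing one resampling unit by the other is not enough.

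**The case against.** The strongest objection is that the defect is read from silence. The economic paragraph does not say that patients are resampled, does not rule out a practice term in the regression, and does not describe the imputation model. This is a condensed article, and such details may stand in a fuller plan. The investigators plainly know about clustering, since it enters the sample size. The clinical paragraph, too, names a mixed model without naming a practice effect.

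Much of this stands. A reader might infer that the protocol prescribes a patient-level bootstrap and that the intervals will be too narrow. The text supports neither statement; it supports only the conditional one. What does not stand is that the point is mere condensation. The paragraph fixes the type of bootstrap, the number of replications, the regression, the time horizon and the graphical outputs. An analyst who followed it literally with those methods in their usual form would leave out the unit of randomisation.

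Three further objections limit the size:
- The ICC of 0.05 belongs to the depression outcome. For costs or QALYs it could be close to zero, where the problem disappears.
- Practices are matched in pairs. Ignoring effective matching makes standard errors too large, which works the other way. How much it offsets depends on how well the matching factors predict costs and QALYs, and the protocol does not tell us.
- At the protocol's own figures the distortion is modest.

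**Conclusion.** The point holds in conditional form. The economic analysis is specified without the unit of randomisation, in a trial whose own sample size needs a design effect of 1.25. Run at patient level, it would give cost and QALY intervals and ICER uncertainty that are too narrow, and acceptability curves that are too certain, whenever the ICC for those outcomes is positive and matching does not cancel it.

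At the borrowed ICC of 0.05 and m = 6, the narrowing is about 11%, coverage about 92%, and 0.95 on an acceptability curve is really about 0.93. The assumed range runs from no effect at ICC 0 to about 18% narrowing and 89% coverage at ICC 0.10. These figures assume equal cluster sizes, approximate normality and no gain from matching.

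It might be tempting to call this a fatal flaw in half of the primary objective. The unstated resampling unit, the unknown ICCs and the modest size at the plan's own figures do not support that. Severity is moderate.

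**What to change.** Amend the Economic evaluation paragraph under Statistical analyses, before the data are analysed:
- Estimate cost and effect differences with a bivariate two-level model that has a random intercept for the randomised unit. That unit is the practice, or the group of practices sharing a nurse.
- Include the same unit in the imputation model.
- Base the intervals, planes and acceptability curves on a cluster-aware bootstrap: two-stage, or resampling that respects the matched pairs. Add a small-sample correction, because plain practice resampling under-covers with 14 clusters per arm.
- Report the estimated ICCs for costs and QALYs.

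The cost is one paragraph and a little more analysis code, with no new data and no change of design. Intervals become somewhat wider: √1.25 = 1.118, so about 12% at ICC 0.05 and m = 6, and less if the ICC is smaller or the matching works.

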#### Process variables and predictors

To identify mechanisms of change and the magnitude of the factors involved, both multilevel mediation models and structural equation models (using path analysis, such as Latent Difference Score (LDS) Models) will be used. Predictors (prognostic factors) and moderators (prescriptive factors) of outcome will be identified using mixed regression, building on the effectiveness models.

### Monitoring

Given the negligible risks of this study, the monitor is an independent researcher of the Primary and Community Care department (ELG) of the Radboud University Medical Centre.

### Harms

We will report all Serious Adverse Events (SAEs) to the sponsor without undue delay after obtaining knowledge of the events. We will report the SAEs through the web portal *ToetsingOnline* to the accredited Medical Ethics Committee that approved the protocol, within 7 days of first knowledge for SAEs that result in death or are life threatening followed by a period of maximum of 8 days to complete the initial preliminary report. All other

SAEs will be reported within a period of maximum 15 days after the sponsor has first knowledge of the serious adverse events.

## Discussion

The aim of this study is to investigate whether BA will be more (cost-)effective than TAU for older adults in primary care. Although BA has been proven to be an effective treatment for depression in adults, the effectiveness of BA delivered by MHNs in older adults, as well as the possible mechanisms of change are not yet clear. The results of the study can be used to improve the quality and availability of treatments for depressed older adults in primary care.

The main strength of this study is that procedures followed in this effectiveness trial closely match the daily practice of PCCs. Therefore the results can be easily generalized to other PCCs. Furthermore, our BA protocol is adapted to a primary care setting, is very easy to train, and therefore easily implemented in other PCCs throughout the Netherlands and abroad.

However, this study also has some limitations that will be taken into account. The main limitation derives from the fact that patients as well as some research assistants, GPs and MHNs are not blinded to patient allocation, due to cluster randomisation. This might influence their judgement of severity of depression of the patients. To prevent biased opinions on whether or not patients (still) have MDD post-treatment, the clinical interview will be performed by an independent research assistant that will be blinded to patient allocation.

Furthermore, we realize that the recruitment of patients in primary care could be challenging [81]. We are aware of the fact that Lasagna’s law, that states that medical investigators tend to overestimate the number of patients available, holds in Dutch primary care research [82]. It might be difficult for GPs to inform depressed older adults about the study in their 10 min sessions. Therefore the only task GPs will have, is to ask patients whether they may be contacted by a research assistant to provide them with more information. From there on, the research assistant will take over.

Lastly, older adults might have difficulties filling in questionnaires due to physical problems such as visual impairments, concentration problems or unfamiliarity with psychological questionnaires. Therefore an independent research assistant, blinded to patient allocation, is available when needed to help patients at home or by phone with the questionnaires.

If proven effective, BA can be a valuable addition to current guidelines for the treatment of older adults with moderate to severe depressive symptoms in primary care.

## Abbreviations

BA: Behavioural Activation
BADS: Behavioural Activation for Depression Scale
BIA: Budget Impact Analysis
BSI − 18: Brief Symptom Inventory-18
CBT: Cognitive Behavioural Therapy
CEA: Cost effectiveness Analysis
DSST: Digit Symbol Substitution Test
EuroQol-5D-5 L: European Quality of Life Self-report Questionnaire
GP: General Practitioner
IPT: InterPersonal Therapy
M.I.N.I. 5.0.0: Mini International Neuropsychiatric Interview
MDD: Major Depressive Disorder
MHN: Mental Health Nurse
MoCA: Montréal Cognitive Assessment scale
PCC: Primary Care Centre
PHQ-9: Patient Health Questionnaire- 9
QALYs: Quality-Adjusted Life-Years
QIDS-SR: Quick Inventory of Depressive Symptomatology
RCT: Randomised Controlled Trial
RRS: Rumination Response Scale
SRS: Session Rating Scale
TAU: Treatment As Usual
TiC-P: Trimbos and iMTA questionnaire on Costs associated with Psychiatric illness
WHODAS: World Health Organization Disability Assessment Schedule 2.0
